### Statistical analysis

A detailed analysis plan will be written and signed off by the Data Monitoring and Ethics Committee for the trial before the analysis commences. Initial analyses will look at summary statistics for all variables, both overall and by randomised group. Summary statistics for continuous variables will be mean, median, standard deviation (SD), lower quartile, upper quartile, and minimum and maximum and will be reported appropriately according to distribution. Summary statistics for categorical variables will be frequency and percentage within each category.

Summary statistics of baseline variables by whether a participant has dropped out of the study will also be examined to determine whether the dropouts had similar characteristics to those who remained in the study at baseline.

After checking the assumptions of proportional hazards, Cox proportional hazards modelling to compare the intervention and control groups, adjusting for severity of cannabis use at baseline (dichotomous – one to three times a week versus four or more times a week), will be carried out for the primary outcome. Robust standard errors will be used to account for clustering by care coordinator. If the assumption of proportional hazards is not fulfilled, alternative modelling strategies will be employed. The secondary outcomes will be analysed using appropriate regression models, separately for data collected at 12 weeks and 18 months. Estimates and 95 % confidence intervals will be presented for the secondary outcomes. In a supportive analysis, all analyses will be adjusted for an indicator as to whether or not the participant was in the pilot trial and for potential baseline predictors of missingness related to outcome. All analyses will be carried out on an intention-to-treat basis using all available data.

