### Group allocation

Following pretrial assessments, consenting clients will be randomised to group, stratified on severity of cannabis use (one to three uses per week, more than three uses per week). A remote, impartial randomisation service will manage the allocation to groups coordinated by the PRIMENT Clinical Trials Unit based at University College London (UCL).

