### Outcome measures

At all assessment interviews the following measures will be performed in addition to the collection of standard demographic information (Fig. 2):

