**Fig. 2 Fig2:**
[figure not shown]
Standard Protocol Items: Recommendations for Interventional Trials (SPIRIT) figure. Overview of the schedule of events

Cannabis use○ The Time Line Follow Back (TLFB) [34] will be used to record self-reported cannabis use over the last 6 months. The TLFB is a retrospective calendar-based measure of daily substance use, with good test-retest reliability demonstrated for cannabis [35]. This will be used to establish eligibility in terms of cannabis use and extent of recent use○ Structured Clinical Interview for the *Diagnostic and Statistical Manual of Mental Disorders, version 4* (DSM-IV) (SCID) part E will be used to assess history of alcohol and substance misuse disorders○ Specimens for urinalysis will be obtained with the threshold set at a level for detecting cannabis use in the previous 28 days (i.e. 50 ng/ml cannabis metabolites)
Psychotic symptoms○ The positive and negative subscales of the Positive and Negative Syndrome Scale (PANSS) [36]. The PANSS is a well-established measure of psychotic symptoms, with strong psychometric properties in terms of validity, reliability, and sensitivity [37]
Service use and health economic analysis○ Client Service Receipt Inventory (CSRI), developed originally by Beecham and Knapp [38] will be used to record clinical service use, medication use, receipt of state welfare, and use of other state-funded services including criminal justice services○ The 12-Item Short Form Survey (SF-12) [39] and the EuroQoL, 5 dimensions (EQ-5D) questionnaire [40] are widely used measures of health status with good psychometric properties [41, 42], which will be used to derive quality-adjusted life years’ (QALYs) data

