### Primary outcome

The primary outcome will be time to relapse. Admission to a psychiatric hospital, crisis resolution team or crisis house, or other acute mental health service will be used as a marker of relapse. The primary outcome will be assessed at 18-month follow-up based on electronic patient records. Dates of admission will be recorded and participants will be followed until they have relapsed, are lost to follow-up, or until the end of the 18-month study period.

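### The primary Cox model is valid and reaches its planned 90% power, but it could cheaply also adjust for baseline PANSS positive score and prior acute service use, for an assumed gain of about 0 to 5 points of power

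*Protocol article*

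**What the plan says.** The Statistical analysis section of the protocol article specifies "Cox proportional hazards modelling to compare the intervention and control groups, adjusting for severity of cannabis use at baseline". Severity is dichotomous and is the same factor on which randomisation is stratified (Group allocation). Clustering is handled separately: "Robust standard errors will be used to account for clustering by care coordinator".

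Further covariates appear only in a supportive analysis. It adds a term for participation in the pilot and, beyond that, adjusts "for potential baseline predictors of missingness related to outcome". The section also promises a detailed analysis plan before analysis begins; it is not shown.

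On the data available at baseline, Outcome measures states: "At all assessment interviews the following measures will be performed". Assessment interviews puts the first interview at consent. The measures include the positive and negative PANSS subscales, and the CSRI, which "will be used to record clinical service use, medication use, receipt of state welfare", among other items.

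The event is defined under Primary outcome: "Admission to a psychiatric hospital, crisis resolution team or crisis house, or other acute mental health service will be used as a marker of relapse". It is taken from electronic patient records over 18 months.

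**The concern.** The trial will hold, before randomisation, a symptom severity score and some record of service use for its participants, and the primary model uses neither. In a Cox model, omitting a covariate that predicts the event attenuates the treatment hazard ratio and lowers power, even when the arms are perfectly balanced. Because allocation is stratified on cannabis severity alone, a chance imbalance in recent acute illness would also go uncorrected in the primary result.

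The supportive analysis is not designed to meet this. It selects covariates because they predict missingness, not because they predict relapse, and the Missing data section expects few missing values for the primary outcome. Either measure could enter by that route, but only incidentally. At stake is a modest amount of power from data that will be collected anyway.

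**Working it through.** **1. Reproduce the plan's figures (Proposed sample size).** Inputs: control relapse about 50%, a reduction of 15 points, hazard ratio 0.63, power 90%, significance level 5% (taken as two-sided), equal allocation.

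- Schoenfeld events: 4 × (1.960 + 1.282)² / (ln 0.63)² = 42.03 / 0.2135 ≈ 197.
- Intervention risk under HR 0.63: 1 − 0.5^0.63 = 0.354. Mean risk: (0.500 + 0.354)/2 = 0.427.
- Participants: 197 / 0.427 ≈ 462, against 460 stated.
- Power at 460: about 196 events, Φ(√196.4 / 2 × 0.462 − 1.960) = Φ(1.278) ≈ 89.9%.
- Clustering: 1 + (4 − 1) × 0.02 = 1.06, and 460 × 1.06 = 487.6, so 488.
- Attrition: 488 / 0.9 = 542.2, so 543, or 544 for two equal arms.

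The 460, 488 and 544 reproduce to rounding, and none of them relies on extra covariates.

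**2. Simulate the Cox model with and without the two covariates.** Each scenario used 10,000 trials of 460 participants, allocated 1:1, with exponential times and administrative censoring at 18 months. Marginal risks were calibrated to 50% and 35.4%. Prior acute use was a yes/no covariate and PANSS positive a standardised normal one. Clustering, attrition and the severity stratum were left out of both models. The covariate hazard ratios and the share with prior acute use are assumptions, because the documents give neither.

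| Share with prior acute use | HR, prior use | HR per SD, PANSS | Power without | Power with | Gain (points) | Estimated HR without → with |
|---|---|---|---|---|---|---|
| 50% | 1 | 1 | 89.2% | 89.1% | −0.1 | 0.629 → 0.628 |
| 50% | 1.5 | 1.1 | 89.6% | 90.4% | 0.8 | 0.628 → 0.624 |
| 50% | 1.5 | 1.25 | 89.3% | 90.6% | 1.3 | 0.629 → 0.621 |
| 50% | 2 | 1.25 | 89.6% | 91.9% | 2.3 | 0.627 → 0.614 |
| 50% | 2 | 1.5 | 90.4% | 93.7% | 3.3 | 0.626 → 0.604 |
| 50% | 3 | 1.5 | 90.6% | 95.6% | 5.0 | 0.624 → 0.589 |
| 80% | 1.5 | 1.1 | 89.6% | 90.2% | 0.6 | 0.629 → 0.626 |
| 80% | 2 | 1.25 | 90.1% | 91.3% | 1.2 | 0.629 → 0.621 |
| 80% | 2 | 1.5 | 90.0% | 92.8% | 2.8 | 0.629 → 0.611 |

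The Monte Carlo standard error of each power is about √(0.9 × 0.1 / 10,000) = 0.3 points. With no treatment effect and covariate hazard ratios of 2 and 1.25, the rejection rate was 4.9% without and 5.1% with the covariates.

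**3. Where the gain comes from.** The standard error of the log hazard ratio did not fall; it was about 0.145 without and 0.146 with the covariates. Power rises because the conditional log hazard ratio lies further from zero. For covariate hazard ratios of 2 and 1.25 with a 50% share:

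- without: |ln 0.627| / 0.145 = 3.22, and Φ(3.22 − 1.96) ≈ 89.6%;
- with: |ln 0.614| / 0.146 = 3.34, and Φ(3.34 − 1.96) ≈ 91.6%, close to the simulated 91.9%.

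**The case against.** The strongest objection is that nothing here is wrong. The model adjusts for the stratification factor, as it should, and its power calculation holds without further covariates. The factor chosen also has support in the document: Background reports a dose-response relationship between cannabis misuse and time to relapse. The document says nothing of the kind about PANSS or prior service use. All of this stands, and it is why the point is optional. It does not make the point a matter left to the analysis plan, because the article itself states the primary covariate and assigns the others to a supportive analysis.

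Three stronger readings are tempting, and the documents do not support them.

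- **That the plan certainly loses power.** The loss depends on a prognostic strength that the documents do not give. It is nil if neither measure predicts admission.
- **That adjustment would cut the variance by 1 − ρ².** With ρ = 0.5, a reader might infer a 25% reduction and power of Φ(3.242 / √0.75 − 1.960) = 96.3%. That is a linear-model result. In the Cox simulations the standard error did not shrink, so the figure does not apply.
- **That the CSRI supplies a baseline value of the primary outcome.** Time to first admission has no baseline value. The CSRI gives a related history variable, taken at interview, whereas the outcome comes from records. The article does not state its look-back or whether acute admissions are coded separately.

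The simulations also leave out the severity term, so the increment over that term specifically has not been tested.

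**Conclusion.** The point holds as a modest efficiency improvement. The primary model is valid and meets its planned 90% power. Adding the two covariates would gain about 0 to 5 points. The gain is about 0.5 to 3 points under weak to moderate prognosis, and about 5 only if prior acute use triples the hazard and PANSS positive raises it by half per standard deviation. With no prognostic value there is essentially no loss (89.2% against 89.1%), and type I error stays near 5%. The size rests on assumed covariate effects, an assumed share with prior acute use, and proportional hazards with exponential times. That the covariate set is narrow and both measures are collected at consent rests on the document alone.

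**What to change.** Before the analysis plan is signed off and before unblinding, specify the primary Cox model as randomised arm, cannabis-severity stratum, baseline PANSS positive score and, where the CSRI look-back allows it to be defined, any prior acute mental health service use (yes/no). Keep the robust standard errors by care coordinator. Fill missing baseline values by simple imputation so that no participant is dropped. Report the severity-only model as a sensitivity analysis.

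The cost is about one line in the analysis plan, with no new data, visits or participants. About 195 expected events (460 × 0.425) easily support four terms. There are small downsides. The hazard ratio becomes conditional on two more covariates and so differs slightly from the planning value of 0.63. Proportional hazards must be checked for the added terms. A few baseline values may need imputing.

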## Background

Cannabis is the most commonly used drug among people with psychosis, with rates of current use around the time of the onset of psychosis regularly recorded as between 35 and 45 %, well above use patterns in same-age, nonpsychotic populations [1, 2]. Continued use following the onset of psychosis is associated with poorer individual outcomes and greater societal burdens. Hazards include delays in remission, suicidal behaviour, violence and homelessness [1, 3, 4]. In prospective investigations in first-episode psychosis, cannabis use is associated with markedly higher relapse rates: an Australian study reported a 51 % relapse rate over 15-month follow-up among substance users (mostly cannabis) compared with 17 % among nonusers [5], accompanied by a threefold difference in inpatient admission rates. Similarly, a Dutch study reported a 42 % relapse rate among persistent cannabis users compared with 17 % among those who never used or stopped round the time of first onset [3]. A dose-response relationship between severity of cannabis misuse and time to relapse was also reported in this study. Studies of comorbid substance misuse among people with established psychosis indicate that people who persist in problematic drug use are heavy users of acute mental health services, are more likely than others with psychotic illnesses to engage in acts of violence, and are less likely to work, sometimes using disability benefits to sustain drug use [6–8]. Thus, if a reduction in cannabis use can be achieved very early in the course of a psychotic illness, this has potential to improve the life experiences and social recovery of young people who develop psychosis, and to reduce the burden on carers, on mental health, criminal justice and welfare services and on the wider society over many years. This is the overall aim of the current study.

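### The primary Cox model is valid as written, but adding the baseline count of cannabis-use days already collected would give a small, free gain in precision; the two severity levels also need closing at both ends

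*Protocol article*

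**What the plan says.** The Statistical analysis section fixes a Cox model for time to relapse, adjusted for baseline cannabis severity as a two-level factor, "one to three times a week versus four or more times a week", with robust standard errors for clustering by care coordinator. Under Group allocation, randomisation is "stratified on severity of cannabis use (one to three uses per week, more than three uses per week". The supportive analysis adds a pilot-trial indicator and baseline predictors of missingness related to outcome. It names no finer cannabis measure.

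Under Outcome measures, the TLFB covers the last 6 months: "The TLFB is a retrospective calendar-based measure of daily substance use, with good test-retest reliability demonstrated for cannabis". Its stated purpose is broader than screening: "This will be used to establish eligibility in terms of cannabis use and extent of recent use".

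The Background says of the cited Dutch cohort: "A dose-response relationship between severity of cannabis misuse and time to relapse was also reported in this study". The Inclusion criteria require use at least once in 12 of the previous 24 weeks.

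**The concern.** The article reports that relapse timing follows the amount of cannabis used, and it collects that amount day by day before randomisation. It then enters the amount in the primary model as a single cut at three uses a week. Someone using on four days a week and a daily user get the same covariate value. Where a prognostic gradient runs within each level, a Cox model that ignores it has somewhat less power for the treatment effect on the primary outcome.

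The wording of the levels raises a second, separate question. The lower level starts at one use a week, but the entry rule admits people who may average less.

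**Working it through.** **1. The plan's own sample size.** Relapse falling from 50% to 35% gives HR = ln(0.65)/ln(0.50) = 0.62, stated as 0.63. The average event probability is (0.50 + 0.35)/2 = 0.425. Two-sided 5% is assumed.
- Schoenfeld's formula at HR 0.63 and 90% power needs 197 events: 197/0.425 = 464.
- Freedman's formula at HR 0.6215 needs 193 events: 193/0.425 = 454.
- The article states 460, so the figure reproduces.
- Clustering: 1 + (4 − 1) × 0.02 = 1.06, and 460 × 1.06 = 487.6, so 488 as stated.
- Attrition: 488/0.9 = 542.2, so 543 against 544 stated.

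None of this depends on the form of the covariate.

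**2. How steep a gradient the article supports.** It gives no size for the dose-response, but the Background gives two contrasts. Under proportional hazards, HR = ln(1 − p₁)/ln(1 − p₀).
- Dutch study, "42 % relapse rate among persistent cannabis users compared with 17 % among those who never used or stopped": ln(0.58)/ln(0.83) = 2.92.
- Australian study, 51% against 17%: ln(0.49)/ln(0.83) = 3.83.

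Both compare users with people who did not use or had stopped. They are probably generous for a contrast between heavy and light current users.

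**3. Power with each form of the covariate.** Simulation with N = 460, treatment HR 0.63, control relapse 50% and 10,000 trials per scenario. Randomisation was 1:1, stratified at 3.5 days a week. Assumptions not in the article: days per week = 0.5 + 6.5 × Beta(0.9, 0.7), a log-linear effect, exponential times, no recall error and no clustering. The continuous model replaced the two-level term.

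| Assumed HR, 7 v 0.5 days/week | Power, treatment only | Power, two-level | Power, continuous | Gain over two-level (points) | Estimated HR, two-level / continuous |
|---|---|---|---|---|---|
| 2.0 | 88.9% | 89.4% | 89.4% | 0.0 | 0.629 / 0.628 |
| 2.92 | 88.7% | 89.5% | 90.0% | 0.5 | 0.630 / 0.628 |
| 3.83 | 87.9% | 89.3% | 90.2% | 0.9 | 0.632 / 0.628 |
| 6.0 | 86.3% | 88.5% | 90.1% | 1.6 | 0.637 / 0.630 |

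With no treatment effect, the rejection rate was 0.049 to 0.055 across both adjusted models, and the mean estimated HR was 1.00.

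The two-level term already captures much of what adjustment can offer. At 2.92 it recovers (89.5 − 88.7)/(90.0 − 88.7) = 62% of the available gain. At 6.0 it recovers (88.5 − 86.3)/(90.1 − 86.3) = 58%.

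**4. Keeping the stratum and adding the count.** A second simulation (1,500 trials per scenario, use days uniform from 12 to 168) compared treatment plus stratum with treatment plus stratum plus use days. The SD is 156/√12 = 45 days, so the range is 156/45 = 3.46 SD.

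| Log-hazard per SD | Implied HR, 168 v 12 days | Power, stratum only | Power, stratum plus count |
|---|---|---|---|
| 0.3 | exp(0.3 × 3.46) = 2.8 | no material difference | no material difference |
| 0.5 | exp(0.5 × 3.46) = 5.7 | 89.2% | 90.5% |
| 0.7 | exp(0.7 × 3.46) = 11.3 | 86.7% | 90.1% |

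The article's contrasts correspond to ln(2.92)/3.46 = 0.31 and ln(3.83)/3.46 = 0.39 per SD, close to the first row.

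**5. The level boundaries.** One use in each of 12 weeks out of 24 meets the entry rule and averages 12/24 = 0.5 a week. If severity is an average over that period, this person is below the lower level in both sections. An average of 3.5 falls in the upper level under Group allocation but in neither level under Statistical analysis. If severity is always a whole number, the two upper levels coincide. The article does not say how severity is measured or rounded.

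**The case against.** The strongest case against is that nothing here is wrong. Adjusting for the stratification factor as used at randomisation is standard practice. Extra prognostic covariates and their functional form are normally settled in the SAP, which is not shown and may already include this one. The dose-response comes from one cited study, with no size or scale given. Most of this stands, and it limits the point to an optional improvement. It does not remove the point, because the article states the form of the covariate and the finer measure is already in hand.

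A reader might go further and infer that the two-level model biases the treatment effect towards the null. The article does not support that. Chance imbalance within strata is not bias under randomisation. The small shift in the hazard ratio is non-collapsibility: a hazard ratio conditional on less is a different quantity. The planned 0.63 matches overall relapse rates of 50% and 35%, so it is not a target conditional on use days.

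A reader might also infer a power loss of 3 points or more. That needs a heaviest-to-lightest hazard ratio near 11, about three times the larger contrast in the Background.

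Finally, adding the count does not resolve the boundary wording, because the stratum term stays in the model. This is correct, so the wording needs its own change.

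**Conclusion.** The primary model is valid, and neither its type I error nor the sample size is in question. Using severity only in two levels forgoes a small amount of precision: 0.0 to 0.9 points of power for gradients of 2 to 3.83 between heaviest and lightest users, and 1.6 points at 6. This rests on the assumed distribution of use, a log-linear effect and error-free TLFB counts. Recall error would reduce the gain, and a non-linear effect could change it. The point is worth taking up because the cost is close to nil, not because the trial depends on it.

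The gap in the severity levels is a separate matter of definition. It affects both the randomisation stratum and the covariate, and how many participants it touches cannot be told from the article.

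**What to change.** In the SAP, before analysis:

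1. Keep the two-level stratification factor in the primary Cox model. Add the number of cannabis-use days in the 24 weeks before baseline, from the TLFB, as one continuous linear covariate fixed in advance.
2. Define the levels as three or fewer and more than three uses a week, in the same words for randomisation and analysis, and state the period and any rounding used. As recruitment is under way, confirm how the randomisation service has classified people averaging under one use, or between three and four uses, a week.

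The cost is one SAP line and one clarified definition. No new data are needed, and sample size and trial conduct do not change.

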### Missing data

It is expected that there will be few missing data for the primary outcome as data for this will be extracted from the participants’ medical records. There is likely to be more missing data for the secondary outcomes as the majority require the participant to be interviewed to complete the measures. For both the primary and secondary outcomes we will check the extent and patterns of missing data and identify predictors of missingness. Multiple imputation or adjustment for potential predictors of missingness related to the outcome will be performed if appropriate.

